#### Qualitative interviews

Using semi-structured interview schedules, qualitative data will be collected on three occasions during the 3-year study (i.e., baseline, 18 months, 36 months) and analysed inductively. For this component of the research, computer-generated randomisation will be utilised to identify 30 participants in the intervention and comparison groups to participate in qualitative interviews. Fifteen participants from each group will be selected in order to account for attrition and possible non-consent, with an aim of completing at least 10 interviews per wave. At each time point, a one-hour individual interview will be conducted by co-investigators who have experience with qualitative research methods.

The baseline qualitative interview will explore participants’ homelessness journey and current experiences related to the outcome variables of interest in this study. Prompts that elicit participants’ hopes or goals for the next year will also be utilised. During the second and third interview (i.e., 18 and 36 months), interviewers will elicit determinants of change, or lack of change, according to stated experiences and goals from the prior interview. Thus, prompts for the second and third interview will be tailored to the unique goals and challenges each participant disclosed during the prior interview. For intervention group participants, the perceived impact of the J2SI Phase 2 intervention on participant’s well-being and in facilitating or blocking goal attainment will be explored.

In addition to interviewing selected study participants, at each time point, intensive case managers and supervisors will be invited to participate in a two-hour focus group. They will be asked to reflect on their experiences delivering the J2SI Phase 2 intervention and how they perceive the intervention is impacting participants. Discussion prompts will be aided by displaying a poster showing the study’s key outcome variables.

All individual and group interviews will be audio recorded (with consent) and professionally transcribed. Immediately following the interview, the interviewer will summarise their impressions of the interview in a memo, which will be shared with the qualitative research team. For each interview, RCT participants (but not intervention staff) will be provided $40 cash (AUD) as reimbursement for their time.

#### Linked administrative data

With consent from study participants, administrative records will be obtained through formal State and Federal data linkage processes. Data will include health service utilisation (e.g., mental health service utilisation, ED presentations, alcohol and other drug treatment services, public hospital and psychiatric hospital admissions), engagement with the justice system (e.g., jail time, court cases, arrests), public housing stays, and use of government-funded homelessness services and government income support payments (see Table 2 for an overview of linked administrative databases to be accessed). Specific ethics processes (beyond university-based human research ethics approval) are required in order to obtain linkage data held by the Australian and Victorian Governments. A Human Research Ethics Committee (HREC) application will be made under Population Health Research Network and Victorian Government protocols to an approved HREC for the Victorian Centre for Data Linkage to undertake the data linkage process (https://www2.health.vic.gov.au/about/reporting-planning-data/the-centre-for-victorian-data-linkage). The study will seek linked administrative data for the three-year period prior to enrolment in the study, the three-year study period, and 3 years beyond completion of the RCT. Information gathered by intensive case managers who are delivering the J2SI Phase 2 program will also be analysed as part of the study.

**Table 2 Tab2:** Summary of Linked Administrative Databases to be Accessed

Dataset name	Short description
Victorian Admitted Episodes Dataset (VAED)	VAED and VEMD contain information pertaining to health outcomes and health service utilisation, and will be used to assist in the estimation of the costs of homelessness and the change in these costs over time.
Victorian Emergency Minimum Dataset (VEMD)	
Client Relationship Information System for Service Providers (CRISSP)	To determine history of family and domestic violence, out-of-home care, and other family history throughout childhood.
Integrated Reports and Information System (IRIS)	To identify access to sexual assault and family violence services.
Housing Integrated Information Platform (HIIP)	To determine participants’ history with the Office of Housing, including public housing tenancies, and how well tenancies are going. For example, if respondents have strikes/notices against them and if they are paying rent on time.
Alcohol and Drug Information System (ADIS)	To understand participants’ alcohol and other drug use and access of treatment services.
Client Management Interface/ Operational Data Store (CMI/ODS)	To ascertain levels of access to different mental health services and to identify if there is a history of identified self-harm/suicide attempts.
Courts Services (Victoria) data	To determine the impact on housing interventions and interaction with the justice system. These databases will be used to assist in the estimation of the costs of homelessness and the change in these costs over time.
Department of Corrections (Victoria) data	
Victorian Police (VicPol) data	
Centrelink data	To ascertain changes in payments and other circumstances in participants’ lives generally and in conjunction with the intervention. Centrelink data is an alternative source to self-report data in a range of areas such as employment, income, Centrelink payment type, and location that we are collecting from participants.
Specialist Homelessness Services data collection (Victoria) from Specialist Homelessness Information Portal (SHIP)	SHIP data contains detailed client information that will provide insight into participants’ utilisation of homelessness services.
National Cause of Death Unit Record Files	The Causes of Death Unit Record Files provide information on the causes of death that occur and are registered in Australia.

### Data management and analyses

All study data and participant information will be stored in password-protected computer files at the UWA Centre for Social Impact, and at Swinburne University of Technology. Access to data will be limited to specific members of the research team. Participant data will not be released outside of the study, unless required by law.

#### Quantitative data analyses

Data will be analysed using SPSS 24 and StataMP 14 (or subsequent versions of these programs). For our primary analyses, we will utilise a modified intention-to-treat method to test study hypotheses using longitudinal survey data and linked administrative data, excluding only those participants who were randomised to the intervention group, completed a baseline survey, but then deemed to have not met the eligibility criteria by the intensive case management team (*n* = 6) or who subsequently withdrew consent (*n* = 1). Individuals randomised to the intervention group but deemed inactive at any time throughout the intervention will still be included in analyses. Intention-to-treat analyses will enable us to take into account the non-random nature of ‘ineligible’ and ‘inactive’ status.

Baseline characteristics of participants will be reported using descriptive statistics, including measures of central tendency and dispersion. Planned analysis includes a combination of statistical tests of difference between the treatment and control groups, and multivariable regression analyses (including random effects mixed modelling) will be used. In adjusted analyses, we will control for the effects of relevant demographic variables, covariates known to be strong predictors of outcomes (e.g., duration of prior homelessness), and variables that reflect any group differences at baseline. We will examine associations between key outcome variables and relevant demographic variables (e.g., age, gender), as well as various aspects of participant trauma history (e.g., type of trauma experienced).

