**Methods/design:**

J2SI Phase 2 is a three-year, mixed methods, multi-site, RCT that enrolled 186 participants aged 25 to 50 years between 07 January 2016 and 30 September 2016 in Melbourne. The intervention group (*n* = 90 recruited) receives the J2SI Phase 2 program, a trauma-informed intervention that integrates intensive case management and service coordination; transition to housing and support to sustain tenancy; and support to build social connections, obtain employment and foster independence. The comparison group (*n* = 96 recruited) receives standard service provision. Prior to randomisation, participants completed a baseline survey. Follow-up surveys will be completed every six months for three years (six in total). In addition to self-report data on history of homelessness and housing, physical and mental health, substance use, quality of life, social connectedness and public service utilisation, linked administrative data on participants’ public services utilisation (e.g., hospitalisation, justice system) will be obtained for the three-year period pre- and post-randomisation. Semi-structured, qualitative interviews will be conducted with a randomly selected subset of participants and service providers at three time-points to explore changes in key outcome variables and to examine individual experiences with the intervention and standard service provision. An economic evaluation of the intervention and associated costs will also be undertaken.

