### Participants and recruitment

Recruitment began in December 2015 and occurred across three catchment areas in inner city Melbourne, Australia (centred on St Kilda, Fitzroy, and North Melbourne). Melbourne is a city of 4.5 million people in the state of Victoria, Australia. Posters advertising the study were displayed at each of the three participating agencies, all of which provide services to men and women experiencing homelessness. All individuals who presented for intake assessment at each of the sites were informed of the project. Interested persons were assessed for study eligibility by a key referring worker who subsequently set up an interview for those deemed eligible, during which written informed consent was obtained and the baseline survey completed. Data collection for the J2SI Phase 2 study commenced in January 2016 and concludes in December 2019.

Recruitment was designed to ensure a minimum of 60 active participants in either group at the end of the baseline survey period. The number of participants in the program was set by budget constraints and the need to ensure that the study had sufficient power to detect differences between groups. Based on attrition rates from the J2SI pilot study, researchers anticipated there would be some intervention group participants who would not engage with the J2SI Phase 2 program but that overall attrition would likely be greater in the comparison group as a result of infrequent contact (i.e., only for follow-up survey administration) and greater loss to follow-up. The study over-recruited, as we anticipated that not all persons volunteering to be part of the study would be assessed as eligible. It was also anticipated that not all persons volunteering to be part of the study would attend the baseline survey or those randomised to the J2SI Phase 2 program would engage.

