### Eligibility and exclusion criteria

Participants are deemed eligible for J2SI program support (and the RCT) if they meet all the following criteria: (1) being aged 25 to 50 years at the time of enrolment (the age group that SHM serve in their homelessness programs); and (2) currently experiencing homelessness (i.e., sleeping rough, in temporary supported accommodation services, in a boarding or rooming house without tenure rights and private facilities, or couch-surfing), or housed for 6 months or less and at direct risk of homelessness due to having received an imminent eviction without a secure housing option available; and (3) having a history of chronic homelessness; and (4) being entitled to Australian welfare payments; and (5) not currently engaged in another long-term homelessness intensive support program. For the purposes of this study, chronic homelessness was defined by J2SI Phase 2 program administrators (i.e., SHM) as having a history of rough sleeping for 12 months continuously and/or at least three episodes of homelessness in the last 3 years.

Otherwise eligible participants are excluded if they meet any one of the following criteria: (1) not being fluent in English, such that an interpreter service would be required (budget constraints preclude interpreter service support); or (2) experiencing unmanaged severe mental illness that precluded provision of informed consent and/or would impede completion of surveys, even with a guardian present; or (3) being deemed by agency staff to pose a safety risk to staff, researchers or the participant themselves.

Among those expressing interest to be involved in the study, 44 did not meet eligibility criteria and were excluded from the study prior to baseline. A further 13 participants were assessed as eligible for the study but did not attend the baseline survey interview, including one enrolee who died prior to the baseline survey (see Fig. 1). This resulted in a total of 186 persons who consented and completed the baseline survey. Post-randomisation, six individuals in the intervention group were excluded from the study as they were retrospectively deemed to not meet eligibility criteria by J2SI Phase 2 support staff, and one individual in the comparison group formally withdrew from the study.

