### Randomisation

After written informed consent was obtained and the baseline survey completed, participants were randomly assigned into either the J2SI Phase 2 (intervention) group or the standard service provision (comparison) group. Although randomisation by computer-generated allocation [46, 47] is often the preferred method, SHM staff informed the research team that some participants in the J2SI pilot study had expressed concern that they felt computer-generated allocation was in some way manipulated to achieve a particular outcome. In response to their concerns, the researchers instead utilised the Sequentially Numbered, Opaque, Sealed Envelope (SNOSE) method [48]. This method is an effective and pragmatic method of randomisation that does not require specialised technology [48].

Due to the nature of the intervention, neither the participants, nor the J2SI Phase 2 support workers could feasibly be blinded to the allocation outcome. However, allocation to the treatment group has not been disclosed to third parties, including other support services.

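### The primary analysis removes six of 90 intervention participants whom unblinded programme staff judged ineligible after randomisation, under a rule worded for that arm only, and the claim that intention-to-treat accounts for this is wrong

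*Protocol article*

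**What the plan says.** Under Participants and recruitment, screening comes before consent and is the same for everyone: "Interested persons were assessed for study eligibility by a key referring worker". Under Randomisation, allocation follows: "After written informed consent was obtained and the baseline survey completed, participants were randomly assigned". The same section says the J2SI Phase 2 support workers could not be blinded.

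The count at that point is clear: "This resulted in a total of 186 persons who consented and completed the baseline survey". The Abstract (Methods/design) gives the split: "90 recruited) receives the J2SI Phase 2 program" for the intervention group and "96 recruited) receives standard service provision" for the comparison group.

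Under Eligibility and exclusion criteria, the article then reports that after randomisation "six individuals in the intervention group were excluded from the study as they were retrospectively deemed to not meet eligibility criteria", a decision it attributes to the programme's support staff. The only loss reported there from the comparison group is one formal withdrawal.

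Quantitative data analyses builds this into the primary analysis. The ineligibility exclusion is worded for people randomised to the intervention who completed baseline "but then deemed to have not met the eligibility criteria by the intensive case management team" (n = 6). Withdrawal of consent (n = 1) is the other exclusion. Participants classed as inactive are kept. The paragraph ends: "Intention-to-treat analyses will enable us to take into account the non-random nature of" ineligible and inactive status.

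**The concern.** An eligibility exclusion made after randomisation can leave the comparison intact if three conditions hold: it rests on information fixed before randomisation, it is judged blind to arm, and it is applied to both arms alike. Here the second fails, because the judges delivered the programme and knew the allocation. The third fails on the wording of the rule. The first is not stated.

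If people like the six also sit among the 96, they stay in the analysis there and are removed only from the intervention arm. The two analysed groups then differ in a way that randomisation did not produce. The same set serves every hypothesis in the Aims, covering housing, mental health, service use, employment, justice contact and costs.

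The intention-to-treat sentence makes this worse. It calls ineligible status non-random, yet the rule just above it excludes on that status. A reader would take it that the problem has been handled.

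**Working it through.** **Counts.** 90 + 96 = 186, which reproduces the stated total. The primary set is 90 − 6 = 84 and 96 − 1 = 95, together 179.

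**Imbalance in ineligibility exclusions.** Intervention 6/90 = 6.7%; comparison 0/96 as described. At the same rate one would expect 0.0667 × 96 = 6.4 in the comparison arm. Fisher's exact test for 6/90 v 0/96 gives p = 0.012. The chance of none in 96 at a rate of 6/90 is (84/90)^96 = 0.0013. This fits a review of one arm only but does not prove it.

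**How far the six can move a binary rate.** Let p be the rate among the 84 who are kept. Restoring the six gives a rate between 84p/90 (none has the outcome) and (84p + 6)/90 (all have it). The width is always 6/90 = 6.7 points.

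| p among the 84 | none of the six | all of the six |
|---|---|---|
| 41% | 38.3% | 44.9% |
| 50% | 46.7% | 53.3% |
| 85% | 79.3% | 86.0% |

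**Against a pilot-sized housing effect.** The Background reports 85% v 41% housed. The nearest whole counts in the primary set are 71/84 = 84.5% and 39/95 = 41.1%, a gap of 43.5 points. Now count all six as unhoused, so that the intervention rate is 71/90 = 78.9%:
- withdrawn comparison participant left out: 78.9 − 41.1 (39/95) = 37.8 points
- that participant counted as unhoused: 78.9 − 40.6 (39/96) = 38.3 points
- that participant counted as housed: 78.9 − 41.7 (40/96) = 37.2 points

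The two-sided z test gives p of about 2 × 10⁻⁷ or less in each case.

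**With no true effect.** Suppose both randomised arms have the same rate p and all six are failures. The intervention rate in the primary set is then 90p/84, overstated by 6p/84. The test on 84 v 95 is taken as two-sided at 5%; this level is my assumption, as the article states none. The normal approximation uses SE = √[p(1 − p)(1/84 + 1/95)].

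| p | overstatement | SE | rejection probability |
|---|---|---|---|
| 41% | 2.9 points | 7.4 points | 6.8% |
| 50% | 3.6 points | 7.5 points | 7.6% |
| 60% | 4.3 points | 7.3 points | 9.0% |

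If the six were successes instead, the bias runs the other way.

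**The intention-to-treat sentence.** It names two statuses. Inactive participants stay in the analysis, so the claim holds for them. Ineligible participants are removed, so analysing the remainder cannot account for why they were removed.

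**The case against.** The exclusion is disclosed and labelled as a modification. Most of the written criteria (age, homelessness history, welfare entitlement, other intensive support) are facts fixed before randomisation. If the six failed one of those, dropping them mainly narrows the population. The plan also keeps inactive participants, 20 of them by the end of the baseline period under Participant retention; they are the larger group and the more obvious route to a flattering result. The research team is described as independent of the programme. Much of this stands as mitigation. It does not repair a rule applied to one arm by unblinded staff. The article does not say which criterion the six failed, and one exclusion ground, safety risk, is a staff judgement. The eligibility decision was the programme staff's, not the research team's.

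Some stronger readings are tempting, but the documents do not support them:
- **That the bias favours the intervention.** Neither reasons nor outcomes are given for the six, so the sign is unknown.
- **That the comparison arm was never reviewed.** This is an inference from the wording of the rule, the identity of the judges and the 6 v 0 split. The text does not say it.
- **That the staff had an interest in the result.** This is plausible from their role, but not documented.
- **That the conclusion would flip.** Hypothetical counts can be found that do so: 51/84 v 43/95 gives p = 0.039 by z test, and 51/90 v 43/96 gives p = 0.105. But Fisher's test on the first pair already gives p = 0.051, and the flip needs all six to be failures. At roughly the same rate as the other 84, restoring them gives 54/90 or 55/90 v 43/96 (p = 0.038 or 0.026). If all six are successes, 57/90 v 43/96 gives p = 0.011.
- **That data up to withdrawal are wrongly discarded.** This concerns one person, and the consent terms are not shown.

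**Conclusion.** The point holds in this form. A stated rule for the primary set breaks the randomised comparison by removing 6.7% of one arm on a judgement that was unblinded, made after allocation and worded for that arm alone. A stated property of the analysis is also false: intention-to-treat does not account for ineligible status here.

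The size is modest. The two extremes for the six are 6.7 points apart on a binary intervention rate. A pilot-sized housing gap of 43.5 points would fall to about 37 to 38 points at the unfavourable extreme and would not be overturned. For smaller effects on other outcomes the exclusion could matter: in the no-effect illustration, nominal 5% error becomes roughly 7% to 9% if all six are failures. These figures rest on assumed outcomes for the six, an assumed two-sided 5% level and pilot rates used only as illustration. The finding itself rests on the article's wording, not on those figures. It should be corrected before the primary analysis, since it affects every hypothesis and the change is small.

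**What to change.** 1. Define the primary set as all participants as randomised, 90 v 96. Include the six with their baseline survey, linked administrative data and any survey waves that consent and availability allow. Treat follow-up that does not exist as missing, handled as for everyone else.
2. Report the 84 v 95 set as a sensitivity analysis.
3. If an eligibility-based set is wanted, apply the written criteria to pre-randomisation data for all 186, judged by someone blind to arm. State which criterion each of the six was held to have failed, and whether the comparison arm was reviewed.
4. Reword the intention-to-treat sentence so that it claims protection for inactive status only, unless the six are restored.
5. Use the withdrawn participant's data up to withdrawal only if the consent terms permit.

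The cost is a change of wording, up to seven more records, and checks on consent and on the linkage approvals described under Linked administrative data. Because the six were excluded from the study, their survey follow-up may be incomplete or absent, and recontact may be needed. The estimate may turn out slightly less favourable.
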